## **Data collection timepoints for secondary outcomes**

1. Peer Support Network satisfaction survey: This will be collected monthly after each Peer Support Network Meeting for a total of 29 months post-baseline.
2. Interviews of enablers and barriers to participation: this will be undertaken during:
  - T2 with Group A (8.5 Months post-baseline), and
  - T4 with Group B (post group B undertaking the intervention at 17 months from baseline).
3. Medical record review: Quality and Outcomes of diabetes care: This will be undertaken during:
  - T1 - (6 Months Post Baseline Group A & B)
  - T4 - Measure effect of training program (PSN, Online Modules, Onsite Support) on group B post group B undertaking the intervention at 17 months from baseline (data collected on both group A & B).
  - T6 - Sustainability of effect of training program on group A 29 months post-baseline, and group B 12 months post commencement of intervention.
4. Service systems assessment - Health Service Characteristics (through focus groups): This will be undertaken once during the study between months 3 and 12 from the start of the study.

[figure not shown]

Figure 4: Data collection timepoints

| Category                        | Description                                                                                                                                         | Validated tool                                        | Number of variables | When or Timeframe                                            | How                                                                  | From whom                                                                                          |
|---------------------------------|-----------------------------------------------------------------------------------------------------------------------------------------------------|-------------------------------------------------------|---------------------|--------------------------------------------------------------|----------------------------------------------------------------------|----------------------------------------------------------------------------------------------------|
| Demographics                    | Characteristics of individuals, their work experience and the site they are employed by                                                             | Research team developed                               | 11                  | T0, T5, T6                                                   | RedCap                                                               | All participants                                                                                   |
| Primary Outcomes                | Diabetes knowledge                                                                                                                                  | Simplified diabetes knowledge scale                   | 20                  | T0, T1, T2, T3, T4, T5, T6                                   | RedCap                                                               | All participants                                                                                   |
|                                 | Confidence in managing diabetes                                                                                                                     | Diabetes Confidence Survey                            | 15                  | T0, T1, T2, T3, T4, T5, T6                                   | RedCap                                                               | All participants                                                                                   |
|                                 | Attitude relating to diabetes                                                                                                                       | Diabetes Attitude Scale (DAS-3)                       | 25                  | T0, T1, T2, T3, T4, T5, T6                                   | RedCap                                                               | All participants                                                                                   |
|                                 | Diabetes management in practice & skill                                                                                                             | Research team developed                               | 9                   | T0, T1, T2, T3, T4, T5, T6                                   | RedCap                                                               | All participants                                                                                   |
|                                 | Diabetes management skillm (foot check)                                                                                                             | Research team developed                               | 10                  | T0, T1, T2, T3, T4, T5, T6                                   | RedCap                                                               | All participants                                                                                   |
| Secondary Outcomes              | Evaluation of Peer Support Network                                                                                                                  | Research team developed                               | 9                   | Monthly after each PSN                                       | RedCap                                                               | Aboriginal Health Workers and Practitioners                                                        |
|                                 | Enablers and barriers of participation, sustainability and effectiveness of the training program                                                    | Research team developed                               | up to 12            | Once during the study at T2 with Group A and T4 with Group B | Semi-structured interview - face to face or zoom                     | A cross section of participants from each discipline; 3 to 5 with a total of up to 15 participants |
|                                 | Diabetes patient behaviour and clinical outcomes                                                                                                    | Assessed against RACGP evidence-based care guidelines | up to 8             | Jan 2018 - 12 month post training intervention (T1, T4, T6)  | Retrospective electronic data extraction                             | Electronic medical records of clients with diabetes in each site                                   |
|                                 | Quality of diabetes care                                                                                                                            | Assessed against RACGP evidence-based care guidelines | up to 35            | Jan 2018 - 12 month post training intervention               | Retrospective electronic data extraction                             | Electronic medical records of clients with diabetes                                                |
| Potential confounding variables | Variables that have the potential to reduce bias in statistical models to give a more accurate estimate of cause and effect of the training program | Based on Directed Acyclical Graphs                    | 5                   | Varied                                                       | RedCap (3 variables are collected in demographic and PSN evaluation) | All participants                                                                                   |
| Health Service Characteristics  | Health service characteristics for delivery of evidence based diabetes care                                                                         | Assessment of Chronic Care Scale                      | up to 50            | Once between months 3 and 12 of the study commencement       | Face to face or zoom                                                 | Multi-D team diabetes or chronic disease team within each service                                  |

Table 3: Summary of data collection methods

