**Onsite Support (minimum of twice over 10-week period):** The OS sessions will occur during the same 10-week period as the e-Learning modules. The OS will be face to face at the primary health care service. The number of OS sessions and what is covered during them will be negotiated between the participants and the OS Facilitator. It is suggested that each service hold a minimum of 2 sessions with the OS Facilitator. OS sessions will be held as a group, if there is more than one AHW/P or multidisciplinary health care providers within the health service. The group sessions will be held with AHW/Ps for the first half of the session and then include multidisciplinary health care providers for the remainder of the session. This format will be assessed and adapted as needed. This format responds to direct feedback during the co-design of the training program.

The OS will be facilitated by a credentialed diabetes educator (CDE) employed by Diabetes SA. The CDE will be a member of the research team.

**Group A:** At the start of month 7, AHW/P and multidisciplinary health care provider participants within the health services randomised to Group A will commence the e-Learning modules and OS, for a duration of 10 weeks. During this time, AHW/Ps from both Group A and Group B will continue to participate in the PSN.

**Wash out period (6 months):** There is a six month 'wash out' period where only the PSN is running. This will occur between Group A and Group B doing the e-Learning modules and participating in the OS.

**Group B:** After the 6-month washout period the participating AHW/Ps and multidisciplinary health care providers within the health services randomised to Group B will commence the e-Learning modules and OS, for a duration of 10 weeks. During this time, AHW/Ps from both Group A and Group B will continue to participate in the PSN.

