## **Data collection timepoints for the primary outcomes**

For the entire study there are seven points in time at which data will be collected. These are labelled T0 (baseline), T1 – T6 in Figure 4 and are referred to in the below outline of data collected. Reason for the training program data collection timepoints are as follows:

- T0- Baseline - groups A & B
- T1 - Measure Effect of Peer Support Network - 6 Months Post Baseline Group A & B (Aboriginal Health Workers and Practitioners only).
- T2 – Measure effect of training program (PSN, Online Modules, Onsite Support) on group A - 8.5 Months post-baseline (data collected on both group A & B).
- T3 – Baseline of group B prior to doing the intervention (data collected on both group A & B), 14.5 months post-baseline.
- T4 – Measure effect of training program (PSN, Online Modules, Onsite Support) on group B post group B undertaking the intervention at 17 months from baseline (data collected on both group A & B).
- T5 – Sustainability of effect of training program on group A 23 months post-baseline, and group B 6 months post commencement of intervention.
- T6 - Sustainability of effect of training program on group A 29 months post-baseline, and group B 12 months post commencement of intervention.

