### **Medical record review (quality of diabetes care and diabetes clinical outcomes)**

Negotiating collaborative agreements with sites prior to study implementation includes the sites agreeing or not agreeing to provide de-identified data from their electronic patient management system (PMS) on their diabetes clients, as defined in section 10.d. As the sites do not all use the same type of PMS, the study will work with the clinic/data manager at each site to determine the best data extraction method for their individual electronic PMS. This will likely require a data extraction report to be written (coded) by the data manager from the site or by the PMS vendor (e.g., Medical Director, Communicare). Data extraction software may also be utilised, such as CAT Plus from PENCS, which compatible with the majority of PMS across Australia. All identifiable data extracted from a PMS using CAT Plus is securely stored within the service and not moved offsite.

The data extraction will be run onsite by an appropriate staff member (as identified by the health service) and saved as a CSV file. The extracted data will be de-identified. The CSV file will be password protected and sent by secure email to the Study Manager.

The study will support the services with the data extraction, as required, including providing reimbursement for their time.

The number of times electronic medical record data is collected will be negotiated with each individual service - ideally, at the beginning, midway and at the end of the project (namely, at T1, T4 and T6(Figure 4)).

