## **Secondary Outcomes**

Provision of evidence-based care and patient biomedical outcomes will be summarised using counts, means and percentages and differences between time collection points reported. Patients will be stratified by for example, age, gender, diabetes type and existing comorbidities.

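### Patient-care outcomes are summarised only as changes between T1, T4 and T6, so the planned analysis makes no use of the months when Group A is trained and Group B is not

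*Protocol*

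**What the plan says.** Section 10.c of the protocol (Data collection timepoints for secondary outcomes) sets the record review under "Medical record review: Quality and Outcomes of diabetes care: This will be undertaken during" and lists T1, T4 and T6. The first is "T1 - (6 Months Post Baseline Group A & B"; the other two are at 17 and 29 months. The paragraph on the medical record review makes the number of extractions negotiable with each service, "ideally, at the beginning, midway and at the end of the project (namely, at T1, T4 and T6(Figure 4". Table 3 gives the period for patient behaviour and clinical outcomes as "Jan 2018 - 12 month post training intervention (T1, T4, T6", by retrospective electronic extraction; the quality-of-care row gives the same calendar span.

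The training timeline is in section 10.b, under Randomisation. "At the start of month 7, AHW/P and multidisciplinary health care provider participants within the health services randomised to Group A will commence" the modules and onsite support, for 10 weeks. Then: "There is a six month 'wash out' period where only the PSN is running". Group B follows, also for 10 weeks. T2 measures the effect "on group A - 8.5 Months post-baseline (data collected on both group A & B", and T3, at 14.5 months, is Group B's own pre-training baseline. Surveys go to both groups at T2 and T3; no record review is listed at either.

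Section 11.a (Secondary Outcomes) says that care provision and biomedical outcomes "will be summarised using counts, means and percentages and differences between time collection points reported", with stratification by patient characteristics. Group allocation is not mentioned there. Yet Objective 2 includes these outcomes in the evaluation of effectiveness, and both the informed-consent section (10.a) and the waiver justification (14.c) give the effect of the training on care and patient outcomes as the reason for collecting the records.

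**The concern.** The trial randomises services, but the stated analysis of patient care does not use the randomisation. A change in a service's results between T1 and T4 mixes any training effect with whatever else altered diabetes care over that time, such as new guidelines, staffing, recording practice or recovery of attendance. The staggered start would remove such trends through a comparison of trained with untrained services over the same months. Both the review dates and the summary in section 11.a pass over that comparison.

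At stake is the patient-care part of Objective 2 and of the hypothesis. A favourable before-after change could be reported as evidence that the training works, and a real effect could be masked by an adverse trend.

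**Working it through.** **1. Reproduce the timeline.** Inputs from section 10.b: Group A starts after 6 months; training lasts 10 weeks, which the protocol's own timepoints round to 2.5 months; the gap is 6 months.

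- T2 = 6 + 2.5 = 8.5
- T3 = 8.5 + 6 = 14.5
- T4 = 14.5 + 2.5 = 17
- T6 = 17 + 12 = 29

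These match the protocol. With 10 weeks taken as 2.30 months the results are 8.3, 14.3, 16.6 and 28.6, which changes nothing below.

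**2. Place the record reviews against the training.**

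| Point | Month | Record review | Months since Group A's training ended | Months since Group B's training ended |
|---|---|---|---|---|
| T1 | 6 | yes | not started | not started |
| T2 | 8.5 | no | 0 | not started |
| T3 | 14.5 | no | 6.0 | not started |
| T4 | 17 | yes | 8.5 | 0 |
| T6 | 29 | yes | 20.5 | 12 |

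The window with A trained and B untrained is 14.5 − 8.5 = 6.0 months. Review points inside it: 0 of 3. Group B's last review before its training is T1, 14.5 − 6 = 8.5 months before that training begins.

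**3. What each contrast estimates.** Let *s* be a steady monthly change unrelated to training, and *d(k)* the effect *k* months after training ends.

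- T1 to T4, both groups together: (17 − 6)*s* = 11*s*, plus an average of *d*(8.5) in A and *d*(0) in B.
- T1 to T6: (29 − 6)*s* = 23*s*, plus an average of *d*(20.5) in A and *d*(12) in B.
- T1 to T3, A minus B: [8.5*s* + *d*(6)] − 8.5*s* = *d*(6).

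In the first two, *s* and *d* cannot be told apart. In the third, *s* cancels on average because services were randomised.

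**4. Is the window in the data?** Table 3 runs from January 2018 to 12 months after training, so all 6.0 months lie inside the record span, and the T4 extract (month 17) is late enough to contain them. Whether each extract holds dated serial values or only the latest value per client is not stated in the text shown; Attachment 14, which lists the variables, is not shown.

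**5. Between-group information at T4.** If measures used a 12-month look-back (an assumption), T4 would cover months 5 to 17: 17 − 8.5 = 8.5 post-training months for A and 0 for B, with B in training for 2.5. At T3 the look-back would cover months 2.5 to 14.5: 6.0 post-training months for A, and neither training nor post-training months for B. T4 is therefore not empty of contrast, but T3 is the cleaner point.

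**The case against.** The strongest reply is that T1, T4 and T6 are dates on which data are pulled, not the limits of the data. A reader might infer from the schedule that the randomised window goes unobserved. The documents do not support that: extraction is retrospective and its span includes months 8.5 to 14.5. This stands, and it narrows the point to the planned summary. Only if extracts prove to be latest-value snapshots would the window be lost.

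A second reply is that section 11.a is a short descriptive statement, that it does not forbid reporting by group, and that an SAP may supply the comparison. That is fair for cut dates and look-back rules. But the protocol does name the contrast, differences between collection points, and it is the wrong one for a claim of effectiveness.

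Third, a reader might infer that T1 is a compromised baseline because the peer network has by then run for six months. For Group A versus Group B it is not: randomisation follows those six months, the network is offered to health workers in both groups, and T1 is the proper pre-training baseline.

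Fourth, eligibility is applied afresh at each review, so a reader might infer that a changing client mix drives the results. It could contribute, but the documents give no figure from which to size it. Repeated cross-sections are a recognised approach to service-level quality of care, and the planned stratification helps in part.

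Finally, the hypothesis places patient benefit in the longer term, and T3 is only six months after Group A's training. This stands as a limit on what T3 can show. T6 has the longer follow-up but no untrained comparator.

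**Conclusion.** The point holds as a fault in the stated analysis. None of the three review points falls in the six months when the groups differ in training, and the protocol commits to time-point differences, so the patient-care results would be before-after changes over 11 and 23 months without a control. That does not support the use of these data to judge effectiveness.

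The conclusion rests on the protocol's own dates and on section 11.a as worded. That the remedy is cheap rests on one unconfirmed assumption: that extracts carry service and test dates.

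Severity is moderate. A reader might infer that the trial's main result is undermined. It is not: these are secondary outcomes with no hypothesis test specified, and the primary survey outcomes are collected from both groups at T2 and T3.

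**What to change.** - **Extraction reports (section 10.c):** require dated values for each service and test. Settle this before sites or vendors write the reports, since dates may not be recoverable later.
- **Cut date:** derive each measure at T3 (month 14.5) from the T4 extract, by the same rules as at T1.
- **Section 11.a, Secondary Outcomes:** state a Group A versus Group B comparison at T3, adjusted for the T1 value and accounting for clustering by service. Carry it out at service level, which agrees with the undertaking in section 14.c to analyse client data in aggregate.
- **Labelling:** call the T1, T4 and T6 differences descriptive, and keep them out of any statement about effectiveness.
- **Optional sensitivity analysis:** restrict to clients eligible at T1, but only if the client ID in section 10.d and the aggregate-analysis undertaking in section 14.c are first reconciled.

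The cost is protocol wording and some extra derivation; no additional extraction is needed if dates are kept. If extracts turn out to be snapshots, either a T3 extraction is needed or the protocol should present these outcomes as descriptive only.

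Limits remain. Group A has about six months of post-training follow-up at T3. The comparison covers only services that supply data, since section 10.a lets services leave the record review at any time and section 10.c makes the number of extractions negotiable. With a potential 17 services (section 14.c), precision may be modest.

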## **Data collection procedures**

### **Demographics, primary outcomes, potential confounding and peer support network evaluation variables**

At each relevant time point of data collection, each participant will receive an email from the Study Manager with a unique URL link to the RedCap Survey. Each time a survey is sent, participants will have up to 14 days to complete the survey. For incomplete surveys, up to three email prompts and one phone call will be used to remind participants to complete the survey. At each data collection time point survey's will be closed after 14 days.

Demographics are collected three times during the study period and will take 5 minutes to complete. The primary outcomes are collected seven times and in total take up to 35 minutes to complete. The peer support network evaluation questions are collected monthly after each PSN session and take approximately 5 minutes to complete.

Surveys can be programmed to be sent automatically on a given date which can be changed as well as sent manually if required.

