## Randomisation

Randomisation will occur at the service level. Enrolled health services will be randomised into Group A and Group B. Randomisation and allocation will be undertaken after six months of providing PSN for all enrolled health service sites and prior to commencement of the training program. All enrolled health service sites will be listed, and a statistician will be responsible for randomizing the health service sites into cluster one (Group A participants) or cluster two (Group B participants) using a block size through a computer program for randomisation.

For the intervention assignment; a cluster crossover randomised trial will be employed in this study, as all participants receive the same intervention based on random service site allocation. Participants in the study sites will know which group they have been allocated after completing six months of the PSN, and before commencing the E-Learning module for group A. The project research team will not be blinded to group A or B allocation, only people analyzing the results will be masked/blinded.

**Peer Support Network (months 1-17):** Only AHW/Ps will participate in the PSN. AHW/P participants from both Group A and Group B will participate in the PSN for the entire duration of the study. The PSN will commence and convene for 6 months prior to Group A doing the e-learning modules and the OS. The PSN will run online via Teams, once a month, for 1.5 to 2 hours duration, and will be facilitated by a credentialed diabetes educator (DNE) who is a research team member.

As this is a pragmatic trial, it is understood that AHW/Ps may not be able to attend all PSN sessions due to competing work and/or personal priorities.

The PSN meetings will not be recorded. The PSN Facilitator will record participation in the network.

**E-Learning Modules (10 weeks):** There are 9 self-paced e-Learning modules. Each module takes approximately 1 hour to complete. Ten weeks have been allocated to complete the e-learning modules. All participants will do the e-learning modules. Services will have agreed to allow their staff to use the work computers and internet and to do the modules during work hours. These can also be done from any computer, at any time. The modules can be left and picked up at the same place for convenience during working hours.

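### T1 and T3 fall at the nominal start of training and stay open for 14 days, with no rule that they close before modules and onsite support begin

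*Protocol*

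**What the plan says.** Four parts of the Protocol bear on this.

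- **Time points (section 10.c, timepoints for the primary outcomes).** T1 is listed as "T1 - Measure Effect of Peer Support Network - 6 Months Post Baseline Group A & B". T3 is listed as "Baseline of group B prior to doing the intervention (data collected on both group A & B), 14.5 months post-baseline". T2 is at 8.5 months and T4 at 17 months.
- **Training start (section 10.b, under Randomisation).** "At the start of month 7, AHW/P and multidisciplinary health care provider participants" in Group A services begin the modules and onsite support, for 10 weeks. A six-month washout follows, and then Group B begins its own 10 weeks.
- **Disclosure (same section).** "Participants in the study sites will know which group they have been allocated after completing six months of the PSN", and before Group A opens the modules.
- **Survey handling (section 10.c, Data collection procedures).** "At each relevant time point of data collection, each participant will receive an email from the Study Manager" containing the survey link. "Each time a survey is sent, participants will have up to 14 days to complete the survey", with reminders by email and then by phone. Closure depends only on elapsed time: "At each data collection time point survey's will be closed after 14 days". The send date is adjustable: "Surveys can be programmed to be sent automatically on a given date which can be changed as well as sent manually if required". No lead time before training is fixed.

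**The concern.** T3 is meant to be Group B's last untrained measurement, and T1 is meant to show what the PSN achieves before any other training. Both meanings require the answers to be given before the modules and onsite support open. The send point, the window length and the training start are all fixed in the protocol, and together they do not secure that order. A later analysis plan cannot recover a pre-training score that was never collected.

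Contamination would be specific to one group at each time point: Group A at T1 and Group B at T3. If training raises scores:

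- Group B's T3 value rises, which shrinks both its T3-T4 change and the A-B difference at T3.
- Group A's T1 value rises, so part of the training effect is counted as PSN effect in the T0-T1 comparison that section 11.a plans.

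T1 has a second exposure. Randomisation and disclosure follow six months of PSN, which is when the T1 survey opens. Confidence and attitude are self-reported primary outcomes, so some T1 answers may come from people who already know whether they start now or wait.

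**Working it through.** **Inputs.** From section 10.c: T1 = 6, T2 = 8.5, T3 = 14.5 and T4 = 17 months; survey window = 14 days. From section 10.b: Group A starts at the start of month 7, which is 6.0 months elapsed; training = 10 weeks = 70 days; washout = 6 months; 9 modules. Assumption: 1 month = 365.25/12 = 30.44 days.

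**1. Reproduce the plan's calendar.** T3 = 6 (PSN lead-in) + 2.5 (T2 minus T1) + 6 (washout) = 14.5 months. T4 = 14.5 + 2.5 = 17 months. Both match.

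**2. Gap between survey and training on that calendar.**
- T1 and Group A start: 6.0 - 6.0 = 0 days.
- T3 and Group B start: 14.5 - (8.5 + 6) = 0 days.

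The whole window then overlaps training: 14/70 = 20% of the block, or 9 x 14/70 = 1.8 modules at an even pace.

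**3. Latest start that still fits before T2 or T4.** The T1-T2 and T3-T4 gaps are 2.5 x 30.44 = 76.1 days. Slack = 76.1 - 70 = 6.1 days. If training starts 6.1 days after the survey is sent, the overlap is 14 - 6.1 = 7.9 days. That is 7.9/70 = 11% of the block, or about 1.0 module.

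**4. Exact durations for Group B.** 70/30.44 = 2.30 months, so Group B starts at 6 + 2.30 + 6 = 14.30 months. T3, sent at 14.5 months, goes out (14.5 - 14.30) x 30.44, or about 6 days, after training has begun. Its window closes near training day 6 + 14 = 20, which is 29% of the block, or about 2.6 modules.

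| Reading | Window days inside training | Training day at closure |
|---|---|---|
| Training starts as late as T2/T4 allow | about 8 | about 8 |
| Nominal months | 14 | 14 |
| Exact 10 weeks + 6 months (T3 only) | 14 | about 20 |

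These figures measure possible exposure, not bias. The protocol gives no effect size, standard deviation or expected distribution of response dates, so the shift in scores cannot be calculated.

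**The case against.** The protocol nowhere says that surveys go out on the day training begins. That follows only from rounded month labels, and the stated intent for T3 is the opposite. Send dates can be changed, and Figures 3 and 4, which could not be read here, may show an order. This is fair: what is established is that no lead time or closing rule exists. But the 6 days of slack in the calendar cannot absorb a 14-day window, so the overlap remains unless someone adds a rule.

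A reader might infer several stronger things that the document does not support.

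- **That T3 is also compromised because allocation is known.** Everyone has known their group since about month 6, by design. The survey window has no bearing on that, so the disclosure point applies to T1 alone.
- **That a fifth of the training effect leaks into the baseline.** This would need every response on the last day and even accrual of the effect. Neither is stated.
- **That the main comparison is biased.** T0 precedes randomisation, and the A-B contrast at T2 uses neither T1 nor T3. Section 11.a names neither as the model baseline, and it calls the PSN-alone analysis descriptive.

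Two limits stand. The modules are already free online (section 14), so no date rule can guarantee an untrained score, although onsite support and the prompts begin only with training. Who is affected at T1 is also unclear: the timepoint list restricts T1 to Aboriginal Health Workers and Practitioners, whereas Table 3 lists all participants. These need reconciling.

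**Conclusion.** The point holds as a gap in scheduling. Followed as written, about 8 to 14 days of the T1 window in Group A and of the T3 window in Group B can fall inside the 70-day training block. With exact durations, the T3 window could close near training day 20. T3 need not then be a pre-intervention baseline for Group B, and Group A's T1 need not reflect the PSN alone. The direction of bias given above assumes that training improves scores and that some participants answer after they have begun; its size is unknown. The range rests on calendar arithmetic from rounded months. The harm is confined to contrasts that use T1 or T3. The change is worth making because it is cheap and protects two of the seven primary-outcome time points.

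**What to change.** 1. State that the T1 and T3 windows must close before modules and onsite support open for the group about to train. Tie this to the actual opening date, because the month labels are rounded. Either send the survey at least 14 days before opening (14/30.44 = 0.46 months, so about month 5.5 for T1 and month 14 for T3 on the nominal calendar), or open training only after the survey has closed.
2. For T1, disclose allocation only after the window has closed. No such rule is possible or needed for T3.
3. Record the completion date of every survey. In a sensitivity analysis, do not treat a Group A T1 response or a Group B T3 response dated after that group's module start as pre-training. Do not exclude T3 responses because allocation is known: that would remove all of them.

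**Cost.** About a two-week shift in the schedule. Sending T1 early means that it reflects slightly less than six months of PSN. Opening training after closure avoids that, but 14 + 70 = 84 days exceeds the 76-day gap, so T2 and T4 would each have to fall about 8 days later relative to T1 and T3. Restricting the date rule to a sensitivity analysis avoids losing late responders from the main analysis in a trial that expects 40 participants and 20 completers.
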